### Sample size calculation

We need 97 subjects per group to complete the study in order to detect an absolute difference of 20% in the number of patients who are within the therapeutic range on the seventh day after starting the treatment. For this calculation, we have set an alpha error of 0.05 and a beta error of 0.2, and we assume that 40% of the patients will be within the desired INR, and expect this to increase to 60% in the experimental group. Given the risk of drop-out, the number of patients per group will increase by 20%, placing the recruitment objective at 120 patients per group.

According to Caraco *et al*.
[31], pharmacodynamic stabilization with warfarin in the standard control group was achieved in 40.2 ± 21 days. For a reduction in ten days in the experimental group and alpha and beta errors of 0.05 and 0.2 respectively, the required number of patients per group will be 70.

### Statistical analysis

All recruited patients will be included in the main analysis, following an ‘intention to treat’ (ITT) strategy. For the ITT analysis, patients lost to follow up will be classified in the following way: 1) patients lost before the seventh day will be considered to be outside the therapeutic range; 2) patients lost before the last visit and that have not reached the stable INR will be considered not to be in stable dosing; 3) all lost visits, the INR will be accounted as being out of the therapeutic range. In addition, we will perform a per protocol analysis on all patients who can be monitored for the three month period planned for the study and who have not missed more than one intermediate follow-up visit.

To compare the analysis variables between both groups, a contrast test of the hypothesis will be appropriate based on the normality of the sample (Kolmogorov-Smirnov test), with a Cox regression for dichotomous variables or Kaplan-Meier curves for representing results whenever possible. A regression model (linear or logistic, as appropriate) will be performed when necessary to correct for possible confounding factors. To determine the difference between the two groups in the proportion of time within the therapeutic range, we will use the linear interpolation method proposed by Rosendaal *et al*.
[27]. Finally, we will perform a regression model stratified by center. The value *P* <0.05 will be established as statistically significant, adjusting for multiple comparisons whenever necessary.

The cost-effectiveness analysis will be performed according to a parallel and independent protocol, with special consideration of the direct costs associated with the health care of these patients.

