## Methods

### Design and setting

The clinical trial was designed as a pragmatic, randomized, parallel two-arm, single blind trial to compare the individualized adjustment of acenocoumarol dosage using a pharmacogenetic algorithm versus the standard adjustment, in patients initiating oral anticoagulation for the treatment of venous thromboembolism. The follow-up period will be three months (Figure
1). The study will be performed in five separate hospital centers in the Community of Madrid (Spain). The recruitment period started in March 2011 and is scheduled to end in the fourth quarter of 2012.

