### Assessment variables

#### Effectiveness variables

##### Primary

• Percentage of patients with an INR within the therapeutic range (INR between 2 and 3) on day seven after the initiation of treatment with acenocoumarol.

• Time from the start of the oral anticoagulant therapy to get a stable INR within the therapeutic range (INR within the therapeutic range for three consecutive measurements for at least two weeks, with a maximum difference between the daily average doses of 10%).

• Number of INRs within the range in the first six weeks of treatment.

• Number of INRs within the range during the three months of the study.

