##### Secondary

• Proportion of time within the therapeutic range, using a linear interpolation method
[27].

• Number of special INR measurements (those that are performed in addition to the scheduled measurements in the program of visits established in this protocol: days 0, 3, 7, 15, 30, 60 and 90).

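### The single per-protocol set depends on three months of attendance, so the day-7 comparison loses valid results to later events and admits patients with no day-7 INR

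*Protocol article*

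**What the plan says.** The Statistical analysis section makes intention to treat the main analysis: "All recruited patients will be included in the main analysis, following an ‘intention to treat’ (ITT) strategy". It then gives rules for missing data, introduced as rules for that analysis. One of them is that "patients lost before the seventh day will be considered to be outside the therapeutic range".

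The per-protocol analysis is additional. Its set has two conditions, both about attendance:

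- "we will perform a per protocol analysis on all patients who can be monitored for the three month period planned for the study"
- "who have not missed more than one intermediate follow-up visit"

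No separate set is given for any endpoint. The first primary variable listed is "Percentage of patients with an INR within the therapeutic range (INR between 2 and 3) on day seven", and the main sample size calculation rests on it. Two other primary variables count in-range INRs over six weeks and over three months. Scheduled INR measurements fall on "days 0, 3, 7, 15, 30, 60 and 90", so day 7 is an intermediate visit.

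**The concern.** Membership of an analysis set for an endpoint should not depend on what happens after that endpoint has been measured. Here it does for day 7. Some of the later events that end monitoring, death above all, are among the trial's own safety outcomes and may be related to treatment.

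Withdrawal also matters. Under Withdrawal criteria the investigator may withdraw a patient on judgement, and the onset of chronic disease leads to exclusion. Under Masking the article accepts that the physician is not blinded. Whether a patient stays in the day-7 per-protocol comparison can therefore be settled by someone who knows both the arm and the day-7 INR.

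The rule fails in the other direction too. It tolerates one missed intermediate visit without saying which, so it admits patients who lack the day-7 endpoint.

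This is the only alternative analysis set the article prints beside intention to treat, so readers will treat agreement between the two as a check on robustness. As defined, the two can agree or differ because of events after day 7.

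**Working it through.** **1. The plan's own figure.** Inputs from Sample size calculation: 40% against 60% in range on day 7, alpha 0.05 (taken as two-sided), power 0.80. Allocation is 1:1 (Randomization). With pooled variance under the null and no continuity correction:

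n = [1.96·√(2·0.5·0.5) + 0.8416·√(0.24 + 0.24)]² / 0.20² = (1.3859 + 0.5831)² / 0.04 = 96.9, so 97 per group.

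This matches the article. The point does not change it.

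**2. How long membership stays open after the endpoint.** From Table 1, the day-7 window closes on day 8 and the final visit falls on days 83 to 97. Membership is decided by a further 83 − 8 = 75 to 97 − 8 = 89 days. The six-week variable ends at day 42, but its per-protocol membership also depends on the visits at days 60 and 90.

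**3. The rule applied to typical patients, day-7 endpoint.**

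| Patient | Day-7 INR | In the set? |
|---|---|---|
| Attends to day 30, dies or is lost before day 90 | Yes | No |
| Attends to day 30, then withdrawn or excluded for chronic disease | Yes | No |
| Misses days 15 and 30, attends the rest | Yes | No |
| Misses only day 7, attends the rest | No | Yes |

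For the last patient, the rules that count missing values as out of range are stated for intention to treat, so the per-protocol handling is not fixed.

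**4. How many valid results could be discarded.** The article gives no rate of loss after day 7. Its only related figure is the 20% drop-out allowance: 0.20 × 120 = 24 per arm. That is the upper bound if exclusions stay within the allowance, and it is reached only if all of them occur after day 7. Assumed rates of 5% to 20% give the range below, with everyone taken to have a day-7 result and loss unrelated to it. Power is Φ[(0.20·√n − 1.3859) / 0.6928].

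| Assumed loss after day 7 | Results discarded per arm | n left | Power |
|---|---|---|---|
| 0% | 0 | 120 | 0.877 |
| 5% | 6 | 114 | 0.860 |
| 10% | 12 | 108 | 0.841 |
| 15% | 18 | 102 | 0.820 |
| 20% | 24 | 96 | 0.796 |

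If, in addition, 5% or 10% of the 96 retained had missed only day 7, about 91 or 86 would have a value (power 0.775 or 0.753).

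**5. Selection, which matters more than power.** At the planned rates, 48 of 120 control and 72 of 120 experimental patients are in range, a difference of 20 points. The extremes arise when those dropped are all in range in one arm and all out of range in the other.

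- 6 dropped per arm: lowest 66/114 − 48/114 = 15.8 points; highest 72/114 − 42/114 = 26.3 points.
- 24 dropped per arm: lowest 48/96 − 48/96 = 0 points; highest 72/96 − 24/96 = 50 points.

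These are arithmetic limits, not forecasts. If later loss is unrelated to the day-7 result, the expected difference stays at 20 points. The direction of any distortion cannot be told from the article.

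**The case against.** The strongest reply is that nothing depends on this set. Intention to treat is the main analysis, keeps every day-7 result and has stated rules for missing ones. The per-protocol set reads as a completer set, in line with a sample size expressed as patients who complete the study, and a three-month rule suits a three-month variable. All of that stands, and it limits the reach of the point. It does not answer the mismatch at day 7, because the article defines the set positively and gives one rule for all endpoints.

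Several stronger readings are tempting, but the documents do not support them.

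- *The set is invalid because it does not check that patients were dosed by their assigned strategy.* The article never says that this analysis is meant to show the effect of the strategy when followed. The trial is pragmatic, the experimental strategy also takes INR into account, and the Anticoagulation monitoring section lets standard practice guide adjustments in both arms. A dose that departs from the algorithm is therefore not clearly a deviation. Some non-compliant patients may also leave through the withdrawal rule, although it is discretionary and concerns the patient's compliance. Adherence criteria may sit in the full protocol.
- *Anyone who bleeds and stops acenocoumarol is removed.* The condition is being monitored for three months. The article does not say that stopping the drug ends monitoring. Death, loss and withdrawal do end it.
- *Twenty-four valid results per arm will be discarded.* Patients lost before day 7 have no result to discard, and the split is not given.

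**Conclusion.** The point holds for the supplementary per-protocol analysis of the day-7 INR and, to a lesser extent, of the six-week variable. The printed rule discards valid results because of later death, loss or withdrawal. For day 7 it also admits patients without the endpoint.

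The number affected is unknown. It lies between 0 and 24 per arm if losses do not exceed the 20% allowance. Loss of precision is small even at the upper bound, because 96 per arm is close to the planned 97. The real cost is selection of unknown size and direction, in which an unblinded investigator can have a part.

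A reader might infer that the trial's main conclusion is at risk. It is not: the intention-to-treat analysis and the sample size do not use this set. The verdict rests on reading the definition as printed. A fuller plan may already give endpoint-specific sets.

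**What to change.** Define per-protocol membership for each endpoint, using only information available up to that endpoint's time point:

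- **Day-7 INR:** patients with an INR in the day 7 (±1) window, whatever their later follow-up.
- **Six-week variable:** apply the attendance rule only to visits up to six weeks.
- **Three-month variable:** keep the present rule.

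Either call the attendance-based analysis a completer analysis or, if a criterion of adherence to the assigned strategy is wanted, define it in advance and as symmetrically as possible in both arms. A criterion that tests the algorithm's dose in one arm and has no real counterpart in the other would remove mainly experimental patients and bring in the post-randomisation selection it is meant to avoid.

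The attendance-based change takes a few lines in the analysis section. INRs and dose changes are already recorded in the case report form, so no new data are needed. The costs are a different set for each endpoint, which must be labelled clearly in the report, and slightly more programming. An adherence criterion would cost more, because the article does not say that the algorithm's recommended dose is recorded.

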### Randomization

The randomization was performed using a masked randomization scheme, in a 1:1 ratio, in blocks of four patients and stratified by center. Based on this scheme, randomization envelopes were created for each center. The patient's code was written on the outside of these envelopes (center and patient codes) and inside the opaque sealed envelope was a card indicating the study group to which the patient was assigned. The envelopes and card were stored in the investigator file.

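### The analysis text assigns Cox regression to dichotomous variables, which does not fit the fixed-visit day-7 primary variable on which the trial was sized

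*Protocol article*

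**What the plan says.** All references are to the protocol article.

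- **Primary variables.** The list opens with "Percentage of patients with an INR within the therapeutic range (INR between 2 and 3) on day seven after the initiation of treatment with acenocoumarol". The second entry is "Time from the start of the oral anticoagulant therapy to get a stable INR within the therapeutic range".
- **Statistical analysis, main comparison.** The section chooses a test according to normality (Kolmogorov-Smirnov) and continues "with a Cox regression for dichotomous variables or Kaplan-Meier curves for representing results whenever possible".
- **Statistical analysis, logistic regression.** It appears only in an adjusting role: "A regression model (linear or logistic, as appropriate) will be performed when necessary to correct for possible confounding factors".
- **Statistical analysis, losses.** A patient lost before day seven is counted as out of range. A patient lost before the last visit without reaching stable INR is counted as not stable.
- **Sample size calculation.** The day-7 variable is sized at 40% against 60%, alpha 0.05 and beta 0.2, giving 97 completing patients per group and 120 recruited. Time to stabilization is sized separately at 70 per group, from a 10-day difference and an SD of 21 days.
- **Center.** Randomization is "in a 1:1 ratio, in blocks of four patients and stratified by center", across five hospitals. In the analysis, center appears in one closing sentence: "Finally, we will perform a regression model stratified by center".

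**The concern.** Cox regression models the time at which an event occurs, with censoring. The day-7 variable has neither: every patient is classified in or out of range at one scheduled visit, and the loss rule fills in the missing ones. If day seven is entered as a common time, all events are tied. The estimate and its standard error then depend on how the software treats ties. If actual visit days were entered instead, the ±1 day window in the study timeline would make the event time reflect scheduling and not INR control.

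The sample size assumes a comparison of two proportions, so the design and the analysis wording do not describe the same test for the variable that set the recruitment target. Logistic regression does not close the gap, because it is reserved for confounder correction when needed. At stake are the planned 80% power, a clear effect measure, and a primary test that is settled before the data are seen.

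**Working it through.** **1. Reproduce the planned sample size.** Inputs from Sample size calculation: p0 = 0.40, p1 = 0.60, alpha 0.05 (taken as two-sided; sidedness is not stated), power 0.80. With pooled variance and no continuity correction:

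n = [1.960·√(2·0.5·0.5) + 0.842·√(0.4·0.6 + 0.6·0.4)]² / 0.20² = 96.9, so 97 per group.

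This matches exactly. Variants give 95 (unpooled), 107 (continuity-corrected) and 77 (one-sided). The 70 per group for time to stabilization matches a comparison of two means: 2·(1.960 + 0.842)²·21²/10² = 69.2, so 70.

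**2. Cox with all in-range events tied at day 7.** Expected events at 97 per group are 97·0.4 = 38.8 and 97·0.6 = 58.2.

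- The Breslow estimate is exactly the risk ratio, 0.60/0.40 = 1.50, with log 0.405.
- The Breslow model-based variance is 1/38.8 + 1/58.2 = 0.0430, SE 0.207.
- The binomial variance of the log risk ratio is 0.6/38.8 + 0.4/58.2 = 0.0223, SE 0.149.
- The SE ratio is 0.207/0.149 = 1.39, so the Breslow SE is 39% too wide.
- The critical value is 1.96·0.207 = 0.406, almost equal to the expected log ratio of 0.405, so power is about 50%.
- Maximizing the Efron partial likelihood at the same expected counts gives a ratio of 1.75.
- The exact discrete method is a conditional logistic analysis, with odds ratio about (0.6/0.4)/(0.4/0.6) = 2.25.

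**3. Operating characteristics by simulation, two-sided 5%.**

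| Analysis of day-7 status | Ratio estimated | Power, 97 per group | Power, 120 per group |
|---|---|---|---|
| Cox, Breslow ties, model-based SE | 1.5 | 50% | 63% |
| Cox, Efron ties, model-based SE | about 1.75 | 77% | 87% |
| Cox, Breslow ties, robust SE | 1.5 | 80% | 87% |
| Chi-square or logistic | 2.25 (logistic) | 80% | 87% |

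Under the null at 97 per group, Breslow with the model-based SE rejects in about 1.1% of trials at a common rate of 40% and 0.5% at 50%. The other analyses stay at roughly 4% to 5%.

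**4. Center.** The article gives no between-center variation, so it is assumed here as an SD on the logit scale over five centers, at 97 per group.

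| Assumed SD | Type I error, unstratified | Type I error, Mantel-Haenszel | Power, unstratified | Power, Mantel-Haenszel |
|---|---|---|---|---|
| 0 | 5.0% | 5.0% | 80% | 80% |
| 0.5 | 4.5% | 5.2% | 81% | 82% |
| 1.0 | 3.0% | 5.2% | 83% | 88% |

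**The case against.** The best defense is that the clause is condensed and garbled. It names Cox and Kaplan-Meier together, never mentions day seven, and is qualified as applying where possible. Stable INR reached or not, and adverse events over three months, are yes/no outcomes with a time axis, and Cox suits both. That may well be what was meant. It does not change what is written: Cox is assigned to dichotomous variables in general, the leading dichotomous variable is a fixed-visit status, and no other main test is clearly named for it.

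Three stronger readings are tempting, and the article does not support them.

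- **That the trial would lose 30 points of power.** This needs Breslow ties, a model-based SE and all events tied at one time. The article specifies no tie method or variance estimator, and other ordinary options lose about 3 points or nothing.
- **That the Cox ratio would be meaningless.** With Breslow ties at one common time it is exactly the risk ratio. What fails in that case is the standard error.
- **That time to stable INR is left to a normality check.** The same clause names Cox and Kaplan-Meier, and this is the primary variable they naturally fit. The fault is that the link is not made explicit.

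On center, the article does commit to a stratified model. Its position at the end of the paragraph may be only list order, and its outcome may be detailed elsewhere.

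**Conclusion.** The point stands as a misassigned method in the stated text, not as an omission. A fixed-visit binary primary variable, sized as two proportions, is matched to a time-to-event model. The cost of following the text literally runs from nothing to about 30 power points at 97 per group, and the reported ratio from about 1.5 to 2.25, depending on software options left open. The worst case is conservative, so the risk is a missed effect and an unclear estimate, not a false positive. These figures assume the planned 40% and 60% rates, two-sided 5% testing and a single common event time.

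Center is secondary. Including the randomization stratum in the main analysis gains almost nothing if centers are alike, and about 4 to 5 power points only under strong assumed heterogeneity.

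This should be fixed before analysis, but it does not put the design or the sample size in doubt.

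**What to change.** Replace the Cox clause with two sentences.

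1. **Day-7 INR in range.** The main analysis is a comparison of proportions stratified by or adjusted for center (Mantel-Haenszel or logistic regression), reported with the risk difference and its 95% CI. Either method serves; one should be named in advance.
2. **Time to stable INR.** Kaplan-Meier curves with a log-rank test or Cox model stratified by center, with patients not stable by the end of follow-up censored.

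The sample size does not change, and the day-7 analysis then agrees with the calculation behind 97 per group. The cost is wording only: no additional data, visits or patients.

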Days 3 and 7 ± 1: The INR will be determined (capillary blood sample analyzed with a portable coagulometer) in both groups, and the acenocoumarol dosage will be adjusted if necessary. Control group patients will follow the dosage indications according to the standard clinical practice and visits will be scheduled for day 3, day 7 ± 1 and day 15 ± 3, depending on the length of the hospital stay. Patients included in the intervention group will have their acenocoumarol regimen readjusted according to the developed algorithm and will be scheduled for visits on day 3, 7 ± 1 and 15 ± 3, depending on the length of the hospital stay.

INR measurements will be performed on both groups and additional visits deemed appropriate for good control of the anticoagulation will be arranged. Any changes made to the dosage and all INR measurements will be recorded in the CRF and the medical records.

Visit days 15 ± 3, 30 ± 5, 60 ± 7 and 90 ± 7: During each visit, and after determining the INR (capillary blood sample analyzed with a portable coagulometer), the dosage will be adjusted. The patient's next scheduled visit will be arranged, and an additional visit will be scheduled if necessary. Adverse events will be recorded during all visits, as contained in “Adverse events” section of this protocol. During the final visit, a complete physical examination will also be performed.

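### The analysis section assigns Cox regression to dichotomous variables and names no comparison of proportions, although the endpoint that sets the sample size is a binary status at the day-7 visit

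*Protocol article*

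**What the plan says.** The first primary effectiveness variable (Assessment variables, Primary) is "Percentage of patients with an INR within the therapeutic range (INR between 2 and 3) on day seven after the initiation of treatment with acenocoumarol". The Sample size calculation section is built on the same variable. It aims to "detect an absolute difference of 20% in the number of patients who are within the therapeutic range on the seventh day", and its rates are given as "we assume that 40% of the patients will be within the desired INR, and expect this to increase to 60% in the experimental group". With alpha 0.05 and beta 0.2 this yields 97 completers per group, raised to 120 for drop-out.

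The Statistical analysis section first refers to a hypothesis test chosen according to a Kolmogorov-Smirnov check of normality, then continues "with a Cox regression for dichotomous variables or Kaplan-Meier curves for representing results whenever possible". Logistic regression appears in the following sentence, for adjustment only: "A regression model (linear or logistic, as appropriate) will be performed when necessary to correct for possible confounding factors". For the day-7 variable the same section sets a missing-data rule: "patients lost before the seventh day will be considered to be outside the therapeutic range". Study procedures allows one day either side for the visit: "Days 3 and 7 ± 1: The INR will be determined".

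**The concern.** In-range status at a single scheduled visit has no event time. A Cox model needs one, and the only candidates are the nominal day 7, which is the same for everyone, or the actual visit day (6, 7 or 8), which reflects scheduling and not response to the dose.

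Read literally, Cox is the only unadjusted method the section attaches to a binary variable. A normality check has no bearing on a yes/no outcome, no test of two proportions is named, and logistic regression is held back for confounder correction. The same variable could then be reported as a hazard ratio in the main comparison and as an odds ratio after adjustment, and neither is the absolute difference used for sizing.

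At stake are the power of the comparison that fixed the sample size, the meaning of its estimate, and a choice of method left open on an endpoint handled by unmasked physicians.

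**Working it through.** **Inputs.** From the Sample size calculation: 40% versus 60%, alpha 0.05, power 80%, 97 per group. From Study procedures: visit on day 7 ± 1. Assumed, because the article does not state them: two-sided testing (which reproduces 97), the handling of tied times, the variance estimator, and the distribution of visit days.

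**1. The plan's own figure.** Two-proportion formula with pooled null variance and no continuity correction:

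n = [1.960·√(2·0.5·0.5) + 0.8416·√(0.4·0.6 + 0.6·0.4)]² / 0.20²
= (1.3859 + 0.5831)² / 0.04 = 96.9, so 97 per group.

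The stated figure is reproduced. Exact binomial power of the chi-square test at 97 per group is 80.7%.

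**2. Cox with every visit on day 7.** Expected in range: 0.4 × 97 = 38.8 and 0.6 × 97 = 58.2, so d = 97 events among N = 194 patients, all at one tied time. The score numerator is 58.2 − 48.5 = 9.7 for either way of handling ties; the variance differs.

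- Breslow, model-based: d × 0.5 × 0.5 = 24.25, so z = 9.7/√24.25 = 1.97.
- Exact (hypergeometric): 24.25 × (194 − 97)/(194 − 1) = 12.19, so z = 9.7/√12.19 = 2.78.

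The Breslow variance is about twice the correct one (24.25/12.19 = 1.99). Its expected z therefore lies almost on the critical value of 1.96, which means about 50% power. The Wald form agrees: ln(1.5)/√(1/38.8 + 1/58.2) = 0.4055/0.2073 = 1.96.

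**3. Cox with actual visit days as the time.** Simulated with the same visit-day distribution in both arms.

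| Analysis at 97 per group, 40% vs 60% | All on day 7 | 15/70/15% on days 6/7/8 | Uniform over days 6–8 |
|---|---|---|---|
| Two-proportion (chi-square) | 81% | 81% | 81% |
| Cox, Breslow ties, model-based variance | 50–51% | 49% | 50% |
| Cox, Efron ties | 78% | 70% | 65–66% |
| Log-rank/exact ties | 81% | 70% | 65–66% |

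A split of 25/50/25% gives about 50% (Breslow score) and 67% (log-rank variance).

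**4. False-positive rate, no true difference.** With all visits on day 7, Breslow Cox rejects in 0.5–1.2% of trials where 5% is intended. With visit days spread equally in both arms, Breslow stays below 3% and Efron or log-rank at about 5–6%, which is 5% within simulation error. Rejection rises only if the visit-day distributions differ by arm. For example, with 50% in range in both arms, 20/50/30% in control and 30/50/20% in the experimental arm give about 7–8% (Breslow) or 13–15% (Efron), while chi-square stays at about 5%. Those splits are illustrations; the article has no data on visit days.

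**The case against.** The strongest reply is that nobody intended Cox for the day-7 variable. The sentence pairs it with Kaplan-Meier curves, a survival pairing that suits time to stable INR, and the next sentence shows that the authors had logistic regression in mind for binary outcomes. That intention is plausible. The text, however, does not link Cox to time to stable INR and does attach it to dichotomous variables, so it needs correcting under either reading.

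A second reply is that the loss to 50% comes from one software setting. This stands. It needs Breslow ties with model-based variance, which the article neither names nor rules out. With all visits on day 7, exact ties lose nothing, Efron loses little, and Breslow with a robust (sandwich) variance also gives 80.7% power and 5.2% type I error by exact enumeration. A reader might infer that power does fall to one half; the documents support only that it could.

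A reader might also infer that the booking day turns into a treatment effect. The documents do not support that. Both arms have the same day 7 ± 1 schedule, no difference in timing is reported, and the article does not say that the actual day would be the time variable. The unmasked physician makes a difference possible, nothing more.

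Nor do early losses show a separate contradiction. A standard Cox set-up would censor a patient lost on day 4, but the section itself scores that patient as out of range.

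Leaving the matter to a statistical analysis plan does not answer the point. This is a stated assignment of method, which such a plan would have to override.

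**Conclusion.** The point holds as a wrong assignment of method. The section gives dichotomous variables a time-to-event model and no comparison of proportions, while the endpoint that fixes 97 per group is a proportion at one visit and was sized as one. The cost if the sentence were followed is conditional. Against about 80% planned power, the result ranges from no material loss (exact ties or robust variance, all visits on day 7), through about 65–70% (Efron or exact ties, actual visit days spread over the window), to about 50% (Breslow ties, model-based variance). Inflated type I error would further require visit days to differ between arms, which is an assumption. The wording is certain; that the day-7 comparison would actually be run as a Cox model is not.

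**What to change.** In the Statistical analysis section, replace the assignment of Cox regression to dichotomous variables with a statement to this effect: day-7 in-range status is compared between arms as a difference in proportions with a 95% confidence interval, accounting for the stratification by centre; every randomised patient is scored once, with losses before day seven counted as out of range as already specified; logistic regression is used for covariate adjustment; Cox regression and Kaplan-Meier curves are reserved for time to stable INR.

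This costs one sentence and needs no change in data collection or sample size. It restores the match between the test and the sample size calculation: 80.7% exact power at 97 evaluable patients per group. It does not settle the separate effect of scoring losses as out of range. If 23 of 120 per arm were lost before day seven, the rates would be 38.8/120 = 32.3% and 58.2/120 = 48.5%, and the two-proportion test would have about 73% power (Breslow Cox about 50%).
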